### Outcomes and follow-up

Follow-up will start from the day of randomization. It will contain two phases: the acute care phase (for the traditional inpatient care, this will last until the discharge from the hospital) and 30 days after the acute care phase. The primary outcome is a composite of all-cause mortality and 30-day readmission. The 30-day readmission will be assessed during the 30 days after the end of the acute phase. Transfers of ACH patients back to the hospital during the acute care phase will be recorded.

Secondary outcomes include individual outcomes in the composite endpoint, fall with injury, medication error, emergency room visit, transfer to ICU, cost, the number of days alive out of the hospital, and quality of life. Fall with injury will be defined based on National Database for Nursing Quality Indicators criteria (Table 5). Medication error is defined in Table 6. Quality of life will be measured by the EQ-5D during the follow-up phone call (Fig. 1).

**Table 5 Tab5:** Definition of fall with injury

Minor	Resulted in application of ice or dressing, cleaning of a wound, limb elevation, topical medication, pain, bruise, or abrasion
**Moderate**	Resulted in suturing, application of steri-strips or skin glue, splinting, or muscle/joint strain
**Major**	Resulted in surgery, casting, traction, required consultation for neurological (e.g., basilar skull fracture, small subdural hematoma) or internal injury (e.g., rib fracture, small liver laceration), or patients with any type of fracture regardless of treatment, or patients who have coagulopathy who receive blood products as a result of a fall
**Death**	The patient died as a result of injuries sustained from the fall (not from physiologic events causing the fall)

Fall with injury will be defined based on National Database for Nursing Quality Indicators (NDNQI) criteria. The primary analysis will consider all fall with injury and sensitivity analyses will be conducted to assess the severity of injury. All the clinical outcomes (e.g., fall and medication errors) are measured in routine practice. The research team will contact the clinical team if there is uncertainty about outcome adjudication

**Table 6 Tab6:** Definition of medication error

Category F	An error occurred that may have contributed to or resulted in temporary harm to the patient and required initial or prolonged hospitalization

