### Statistical analysis

Logistic regression will be performed to assess the primary outcome. Analysis will be performed on all eligible patients who provide consent, are randomized, and start the intervention, following the intention-to-treat (ITT) principle. Cox proportional hazards regression analysis will also be performed to assess time-to-event; cumulative incidence curves will be plotted. If there is cross-over between treatment arms, a “per-protocol” analysis will be performed. In this per-protocol analysis, the ACH group would consider all patients who are randomized to ACH, with the follow-up censored at the time of crossing over to the control group; similarly, the control group would consider all patients who are randomized to control, with the follow-up censored at the time of crossing over to ACH. When analyzing continuous outcomes (i.e., cost and days alive out of hospital), a generalized linear model will be used, assuming a γ distribution with a log link, given the skewed nature of the data. When examining the long-term time-to-event outcomes beyond 30 days, a Cox proportional hazards model will be used when it may be necessary to account for censored data.

Because the baseline and outcome data will be obtained from the EHR, no significant missing data is expected. The study coordinators will check with patients during the end-of-study phone call regarding outcome events in case patients receive care outside of the study sites (Additional file 8). However, such events are anticipated to be rare in this patient population. In a previous trial of a HaH program, only 2 out of 91 patients received care outside the study sites [3].

Exploratory analyses such as machine learning approaches using causal tree will be performed to examine the heterogeneous treatment effect (HTE), i.e., which patients might benefit most from the intervention. Exploratory analyses will be performed stratified by acute and restorative phases.

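### The per-protocol analysis censors at an undefined cross-over without adjustment, so it can be biased, towards non-inferiority if ACH crossers are the sicker patients

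*Protocol article*

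**What the plan says.** All references are to the protocol article.

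- **Primary analysis** (Statistical analysis): "Logistic regression will be performed to assess the primary outcome". The analysis set is labelled intention-to-treat: "Analysis will be performed on all eligible patients who provide consent, are randomized, and start the intervention, following the intention-to-treat (ITT) principle". A Cox model is planned in addition.
- **Per-protocol analysis** (same section): "If there is cross-over between treatment arms, a “per-protocol” analysis will be performed". For the home-care arm the rule is: "the ACH group would consider all patients who are randomized to ACH, with the follow-up censored at the time of crossing over". Crossing here means a move into hospital care. For the other arm it is: "the control group would consider all patients who are randomized to control, with the follow-up censored at the time of crossing over to ACH". No weighting or other handling of the censoring is given, and the model for this analysis is not named.
- **Readmission window** (Outcomes and follow-up): "The 30-day readmission will be assessed during the 30 days after the end of the acute phase".
- **Transfers** (Outcomes and follow-up): "Transfers of ACH patients back to the hospital during the acute care phase will be recorded". The Intervention section describes escalation to hospital as a transfer within the ACH model and reports acute-phase transfers as adverse events. It counts re-admission in the restorative phase as an outcome event. It then mentions cross-over separately, calls it rare and says that it will be recorded. It does not define the term.

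**The concern.** Plain censoring is safe only if, within each arm, patients who cross have the same later risk as those who do not. A move from home care to hospital may well follow clinical worsening, and a move from hospital to home care may well follow stability or preference. The documents give no data on either.

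Two features of the plan sharpen the problem. First, the readmission part of the endpoint opens only when the acute phase ends. A patient who crosses during that phase can contribute only a death before crossing. Second, the line between a transfer and a cross-over is not drawn. If acute-phase transfers were handled as cross-overs, the patients for whom home care proved insufficient would be the ones removed.

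In a non-inferiority trial the per-protocol result is read as a check on the intention-to-treat result. Agreement between the two reassures little if the second can lean in the same direction as a false claim.

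**Working it through.** **Inputs from the protocol article (Sample size, Interim analysis).** Control risk 30%; ACH risk 30% under the alternative; margin odds ratio 1.909, which is 45% against 30%; one-sided alpha 0.025; 180 per arm; 80% power; one interim look with rho = 3.5.

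**The plan's own figure.** The log-odds-ratio formula is n per arm = (z₀.₉₇₅ + z₀.₈₀)² × [1/(p₁q₁) + 1/(p₂q₂)] / (ln 1.909)². With p₁ = p₂ = 0.30 this is (1.960 + 0.842)² × (2/0.21) / 0.6466² = 178.8. A score version gives 179.5. Adding one look at half the information (interim alpha 0.0022, final critical z 1.974) gives 180 per arm with power 0.800. The stated 360 reproduces.

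**Assumed inputs.** The documents give neither a crossing rate nor the risk of crossers. I take a fraction c of the ACH arm crossing in the acute phase, with event risk r, for c = 2%, 5% and 10%. The true ACH risk is set at the margin (45%), where non-inferiority should be declared 2.5% of the time.

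**Formulas.** Crossers leave the analysis early, so the apparent ACH risk is p′ = (0.45 − c·r)/(1 − c) on 180(1 − c) patients. The apparent odds ratio is OR′ = [p′/(1 − p′)]/(0.30/0.70). The probability of declaring non-inferiority is Φ[(ln 1.909 − ln OR′)/SE − 1.96], with SE² = 1/[180(1 − c)p′(1 − p′)] + 1/(180 × 0.21). The interim look is ignored.

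**Example, c = 5%, r = 80%.** p′ = (0.45 − 0.04)/0.95 = 0.432; OR′ = 1.772; SE = 0.224; (0.6466 − 0.5719)/0.224 − 1.96 = −1.63; Φ = 0.052.

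**One-sided error, crossing in the ACH arm only, crossers dropped:**

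| ACH crossing | r = 30% | r = 45% (average) | r = 60% | r = 80% |
|---|---|---|---|---|
| 2% | 2.2% | 2.5% | 2.8% | 3.4% |
| 5% | 1.8% | 2.5% | 3.5% | 5.2% |
| 10% | 1.2% | 2.5% | 4.8% | 10.3% |

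**Both arms crossing at 5%, ACH crossers at 80% risk.** Here the control risk becomes (0.30 − c·r)/(1 − c), and both arms have 171 patients.

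| Risk of control crossers | Apparent odds ratio | One-sided error |
|---|---|---|
| 15% | 1.71 | 7.1% |
| 30% (average) | 1.77 | 5.1% |
| 80% | 2.02 | 1.4% |

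The direction therefore depends on who crosses in each arm. There is no bias when crossers have the average risk of their arm.

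**If censored patients were kept in a logistic model as non-events.** The apparent ACH risk is then 0.45 − c·r on all 180 patients. At 5% ACH crossing the error is 6.1% at average risk and 11.0% at 80% risk. The protocol does not state this coding; the figures show only why it should be ruled out.

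**The case against.** The strongest reply is that the protocol already treats transfers and cross-overs as different things. Transfers are part of ACH and are reported as adverse events; cross-over comes later, in a separate remark, and is called rare. On that reading, patients who escalate to hospital stay in follow-up and the censoring touches few people. This is the more natural reading and it largely stands, but the text never says so, and the analysis depends on it.

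A reader might infer that the rule simply removes those for whom home care failed and so always favours ACH. The documents do not support that. They do not equate cross-over with failure. Restorative-phase re-admissions count as events. The control arm has the same censoring rule, so the net bias can go either way.

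A reader might also infer error rates of 20-32%. Those need 10% crossing at 60-80% risk together with coding censored patients as non-events in a logistic model. The protocol states no such coding, its censoring wording fits the Cox model named just before, and 10% sits poorly with rare.

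It is also fair that the analysis is supporting and conditional, that the Discussion names intention-to-treat as primary, and that the analysis plan, which is not shown, may add sensitivity analyses. The Statistical analysis plan section does say, however, that it will include the analyses described, so the plain censoring rule carries forward unless it is changed.

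**Conclusion.** The point holds in conditional form. The protocol fixes unadjusted censoring at cross-over in both arms and does not separate cross-over from acute-phase transfer. If crossing depends on prognosis, the supporting per-protocol result is biased, and an acute-phase crosser is removed before any readmission can count. The bias favours non-inferiority if ACH crossers are above average risk and control crossers are not.

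With ACH crossing only, the effect is slight at 2% crossing and becomes material from about 5%. It rests on assumed crossing rates and crosser risks. Nothing in the protocol makes the non-inferiority conclusion depend on this analysis, so these error rates describe how far the check can be trusted, not the error of the trial's primary test. The point deserves a correction but does not threaten the main result.

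**What to change.** 1. State that, for the analysis, acute-phase transfers of ACH patients to hospital are not cross-overs, and that these patients stay in follow-up with all events counted. Define what is a cross-over in each arm.
2. For true cross-overs in either arm, run the per-protocol analysis as a time-to-event analysis with inverse-probability-of-censoring weights, using baseline covariates and acute-phase status, if numbers permit. State that censored patients will not be coded as non-events in the logistic model.
3. Add a conservative sensitivity analysis that keeps post-crossing events or counts ACH-to-hospital cross-overs as events.

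The cost is a few sentences in the protocol or analysis plan and a little programming; transfers and cross-overs are already to be recorded. The per-protocol estimate may become less precise or less favourable to ACH. With very few cross-overs the weights may not be estimable, and the sensitivity analysis in item 3 then carries the check.

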### Sample size

This randomized non-inferiority trial is designed to assess the non-inferiority of the defined ACH model compared to traditional inpatient hospital care. Based on preliminary analyses, we expect that the event proportion of the composite endpoint in the traditional brick-and-mortar hospital care arm will be approximately 30%. Additionally, we expect that the event rate in the ACH arm under the alternative hypothesis will be 30%. Sample size is based on the one-sided score test statistic for the non-inferiority test for an odds ratio of proportions. Given a non-inferiority odds ratio of 1.909, one-sided alpha of 0.025, and an interim analysis (defined under Interim Analysis), a sample size of 360 (180 per arm) is required to achieve 80% power. A non-inferiority margin expressed as an odds ratio of 1.909 with a 30% event rate in the traditional inpatient care arm is equivalent to a relative risk ratio of 1.5, a 45% event rate in the ACH arm, as the non-inferiority margin. EAST (Cytel) software was used for all sample size calculations.

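### The gamma/log-link model fixed for days alive out of hospital does not suit a capped outcome that is 0 for a death during the index hospital stay; if those zeros are excluded, an acute-phase mortality difference drops out of this secondary outcome

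*Protocol article*

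**What the plan says.** Under Outcomes and follow-up, the protocol article lists among the secondary outcomes "transfer to ICU, cost, the number of days alive out of the hospital, and quality of life". The Statistical analysis section gives cost and days alive out of hospital one shared model: "When analyzing continuous outcomes (i.e., cost and days alive out of hospital), a generalized linear model will be used". The same sentence then names the family, the link and the reason for them: "assuming a γ distribution with a log link, given the skewed nature of the data". It does not say in which direction either outcome is skewed, and the article gives no rule for zero values.

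Three other statements determine what the outcome looks like:

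- **Start of follow-up.** "Follow-up will start from the day of randomization", so deaths in the acute phase count.
- **End of follow-up.** Two periods make up the window: "the acute care phase (for the traditional inpatient care, this will last until the discharge from the hospital) and 30 days after the acute care" has ended. The count therefore has an upper limit.
- **Event rate.** The Sample size section expects that "the event proportion of the composite endpoint in the traditional brick-and-mortar hospital care arm will be approximately 30" per cent, and for the other arm "we expect that the event rate in the ACH arm under the alternative hypothesis will be 30" per cent.

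The analysis set is all eligible, consented, randomized patients who start the intervention, described as intention to treat. The Statistical analysis plan section says the later plan will include all the analyses described in the article, so this choice of model is meant to carry forward.

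**The concern.** A gamma distribution describes strictly positive, right-skewed data without an upper limit. Cost behaves that way. Days alive out of hospital does not: it has a ceiling, most patients should reach it, and its tail runs down towards 0. A patient who dies before leaving the hospital scores exactly 0, a value the gamma distribution cannot accommodate.

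The zeros matter more than the shape. The outcome is meant to count against both death and time in hospital, and its zeros are mostly the earliest deaths. An analyst whose software rejects zeros must leave those patients out, add an arbitrary constant, or change the model after seeing the data. Leaving them out removes the patients the outcome is meant to penalize most, and breaks the stated analysis set.

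**Working it through.** **Scale.** The article gives no figure for this outcome, so its sample size is used only to set the scale. For 30% vs 30%, margin odds ratio 1.909 and one-sided alpha 0.025, the Wald formula gives (1.960 + 0.842)² × [2/(0.3 × 0.7)] / (ln 1.909)² = 178.8 per arm. A score version gives 179.5, hence 180 per arm. The stated total of 360 reproduces.

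**Step 1: shape.** With 30% expected to die or be readmitted, about 100% − 30% = 70% should be at the ceiling. This was simulated over 30 post-acute days with the composite held at 30%. The splits are assumptions, since the article gives none: acute-phase death 0–3%, post-acute death 2–7%, the rest readmitted for about 5 days on average.

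| Quantity | Simulated outcome | Gamma with the same mean and SD |
|---|---|---|
| At the 30-day maximum | about 70% | not applicable |
| Skewness | −2.9 to −3.9 | +0.2 to +0.5 (2 × SD/mean) |
| Probability above 30 days | 0 | about 31% (1% acute-phase deaths) |

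The left skew remains with no acute-phase deaths at all (−3.4).

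**Step 2: value at zero.** For shape k, the gamma log-density contains (k − 1) ln y. At y = 0 this is −∞ for k > 1 and +∞ for k < 1. The unit deviance, 2[(y − μ)/μ − ln(y/μ)], diverges as y approaches 0: with μ = 25 it is 4.5 at y = 1, 18.3 at 0.001 and 32.1 at 0.000001. In practice, R's glm with a Gamma family stops with an error on non-positive values. The statsmodels Gamma GLM in Python returned coefficients with 3 zeros present, but an infinite log-likelihood.

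**Step 3: will zeros occur?** The documents do not give acute-phase mortality. If it is π in all patients and each such death scores 0, the chance of at least one zero among 360 is 1 − (1 − π)^360:

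- π = 0.5%: 1 − 0.995^360 = 84%.
- π = 1%: 1 − 0.99^360 = 97%.

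With no acute-phase deaths, zeros would be rare (about 0.1% of patients in the simulation).

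**Step 4: zeros excluded.** Suppose both arms have the same mean m among acute-phase survivors, and acute-phase ACH deaths also score 0. The arm mean is then (1 − π)m. The ratio of means over all patients is (1 − π₁)/(1 − π₀); with zeros excluded it is m/m = 1, ignoring rare post-acute zeros.

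| Assumed acute-phase mortality | Ratio, all patients | Ratio, zeros excluded |
|---|---|---|
| 0.5% vs 1% | 0.990/0.995 = 0.995 | 1.00 |
| 1% vs 3% | 0.97/0.99 = 0.98 | 1.00 |
| 2% vs 6% | 0.94/0.98 = 0.96 | 1.00 |

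Simulation agrees. At 1% vs 3%, with the composite held at 30% in both arms, the ratio was 0.981 with all patients and 1.002 with zeros excluded. At 2% vs 6% it was 0.960 and 1.000, and with zeros excluded the 95% interval covered the true ratio in only 34% of trials.

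**Step 5: zeros kept.** Quasi-likelihood fitting (gamma variance function, Pearson scale) uses only the mean and variance. With arm as the only covariate, it estimates the ratio of arm means. Over 2,000 simulated trials of 180 per arm:

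| Acute-phase deaths | Mean ratio | 95% coverage | Rejection under no difference |
|---|---|---|---|
| 1% vs 1% | 1.000 | 95.2% | 4.8% |
| 2% vs 2% | not recorded | 94.4% | 5.7% |
| 2% vs 6% | 0.960 (true 0.959) | 94.3% | not applicable |

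**The case against.** The strongest reply is that a log-link mean model with zeros retained works. Step 5 bears this out: despite skewness of about −3, coverage and error rates are close to nominal. The shape mismatch alone therefore does little harm to the comparison of arms, and this stands. The harm needs zeros to be rejected or left out, which depends on the software.

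Nor does the article say that zeros will be dropped. Its analysis set and its stated intention to use all available data point the other way, and a refusal by R is a visible failure. The analysis plan could still settle how zeros are handled. All of that is fair. But the article names the distribution for this outcome and says nothing about zeros, so the plan as written invites an improvised repair once the data are in.

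A reader might infer two stronger claims that the documents do not support:

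- **That excess early deaths would become invisible in the trial.** They would not. All-cause mortality is part of the primary composite, each component is also a separate secondary outcome, and all adverse events go to the data and safety monitoring board.
- **That exclusion would fall unequally on the arms by design**, because an ACH patient who dies at home would have a positive count. That holds only if acute-phase days at home count as out of hospital, which the article does not say. The calculation in Step 4 assumes the opposite, so it cannot support this claim.

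Finally, 2% vs 6% is probably high for patients screened for clinical stability, with those needing intensive care excluded. It illustrates the mechanism and is not a forecast.

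**Conclusion.** The point holds, within limits. The model named for days alive out of hospital is the wrong family for a capped, left-skewed outcome with possible zeros, and its likelihood is undefined for a patient who dies during the index stay. The size of the problem depends on what happens to the zeros:

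- **Excluded:** a mortality difference in the acute phase disappears from this outcome, with the ratio moving from 0.98 to 1.00 (1% vs 3%) or from 0.96 to 1.00 (2% vs 6%). At 0.5% vs 1% the loss is only from 0.995 to 1.00.
- **Kept by quasi-likelihood:** the ratio of means is essentially correct, with about 94–95% coverage.

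The mortality rates, readmission stays and splits of the 30% are assumptions; the ceiling and the expected 70% event-free follow from the article. One secondary outcome is affected. The primary non-inferiority conclusion and the mortality outcome are not. The change is still worth making, because it is cheap and removes a decision that would otherwise be taken after the data are seen.

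**What to change.** Restrict the gamma/log-link model to cost. For days alive out of hospital, compare mean days between arms with robust or bootstrap standard errors, adjusted for site. State that every patient in the analysis set is retained and that deaths before leaving hospital count as zeros. Add a site-stratified rank or proportional-odds analysis as a sensitivity analysis.

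This takes a sentence or two in the protocol or analysis plan and needs no further data or patients. It should be done before the database closes, since the article allows no changes after that. The downside is that the effect is then reported as a difference in days and not as a ratio.

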### Interim analysis

An interim analysis will be performed when at least 50% of patients complete follow-up. We plan for this interim analysis to consider cost, resources, and meaningfulness of the trial and the interim analysis could call for potential termination or early declaration of success. Using the same composite endpoint and analysis plan as the primary endpoint, if the odds ratio of event proportions between the two arms is > 1.984, then the study will be stopped because one arm seems to be more beneficial than the other. Otherwise, the study will continue to full accrual and the final analyses will be conducted as described. The rho family spending function with rho=3.5 was used.

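### The interim rule fixes the stopping odds ratio at 1.984 for any look from 50% onward, although the cited rho=3.5 spending function gives a lower bound at a later look

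*Protocol article*

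**What the plan says.** The Interim analysis section of the protocol article makes three statements about one look.

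- Timing: "An interim analysis will be performed when at least 50% of patients complete follow-up". This sets a minimum and no maximum.
- Decision: "if the odds ratio of event proportions between the two arms is > 1.984, then the study will be stopped". In every other case the trial goes on to full accrual.
- Derivation: "The rho family spending function with rho=3.5 was used". The section does not say whether alpha, beta or both are spent, and it does not say that the threshold is recomputed at the actual look.

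The Sample size section supplies the planning values: a control event proportion of about 30%, described as an expectation; the same 30% in the ACH arm under the alternative; a margin given as "Given a non-inferiority odds ratio of 1.909"; a "one-sided alpha of 0.025"; and 180 patients per arm for 80% power.

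**The concern.** A spending function ties the boundary to the amount of information at the look. A fixed odds ratio does not move with information. The section uses the fixed number as the decision rule, allows the look to come at any point from 50% onward, and names a spending function as the basis of the design. If the look comes late, or the event rate is not the planned one, the number in the text may no longer be the boundary that the named function gives. The monitoring board could then continue a trial that the cited design would stop, or stop one that it would continue.

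**Working it through.** **Inputs.** From Sample size: 30% events in each arm under the alternative, margin OR 1.909, one-sided alpha 0.025, power 80% (beta 0.20), 180 per arm. From Interim analysis: rho = 3.5, look at 50% or later, threshold OR 1.984. Assumptions: the function spends beta, the odds ratio is ACH over control, the information fraction is t = (patients per arm)/180 unless stated otherwise, and the normal approximation holds for the log odds ratio.

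**Sample size, reproduced.** Fixed design: n per arm = 2 × (1/0.21) × (1.960 + 0.842)² / (ln 1.909)² = 178.8. Adding one rho=3.5 look at t = 0.5 gives a total N of 359.4 (beta spending only), 359.8 (alpha only) or 361.7 (both). All are close to 360, so N does not reveal which error is spent.

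**Threshold, reproduced.** With n patients per arm and event rate p:

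- beta spent = 0.20 × t^3.5
- SE = √(2 / (n p (1 − p)))
- bound = exp(z × SE), where z is the upper normal quantile of the beta spent

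At n = 90, t = 0.5, p = 0.30: beta spent = 0.0177, z = 2.104, SE = 0.3253, bound = exp(2.104 × 0.3253) = **1.983**, against the stated 1.984. The alpha-spending non-inferiority bound at the same look is exp(ln 1.909 − 2.847 × 0.3253) = 0.756, so 1.984 is not that bound.

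**Later looks, 30% events.** The chance of stopping equal arms under the fixed rule is 1 − Φ(ln 1.984 / SE); under the spending bound it equals the beta spent.

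| Look | n per arm | SE | Spending bound (OR) | Stop if OR = 1, spending | Stop if OR = 1, fixed 1.984 |
|---|---|---|---|---|---|
| 50% | 90 | 0.325 | 1.983 | 1.77% | 1.76% |
| 55% | 99 | 0.310 | 1.840 | 2.47% | 1.36% |
| 60% | 108 | 0.297 | 1.723 | 3.35% | 1.05% |
| 70% | 126 | 0.275 | 1.543 | 5.74% | 0.64% |

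**At a true OR of 1.909, 60% look.**

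- Fixed rule: 1 − Φ((ln 1.984 − ln 1.909)/0.297) = 1 − Φ(0.130) = 44.8%.
- Spending bound: 1 − Φ((ln 1.723 − ln 1.909)/0.297) = 1 − Φ(−0.345) = 63.5%.
- With 45% events in the ACH arm in the SE (0.2855), the figures are 44.6% and 64.0%.

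The two rules therefore disagree in about 19% of such trials. With equal arms at the same look they disagree in 3.35% − 1.05% = 2.3%.

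**Fewer events, 90 per arm.** The 20% rate is an assumption, not a document figure. SE = √(2/(90 × 0.16)) = 0.3727, and ln 1.984/0.3727 = 1.838, so the fixed rule stops equal arms 3.3% of the time (3.6% by exact binomial calculation). The spending bound here depends on what information means:

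- By patients, t = 0.5 and the bound is exp(2.104 × 0.3727) = 2.19.
- By statistical information, t = 0.5 × 0.16/0.21 = 0.38, beta spent = 0.0068, and the bound is exp(2.466 × 0.3727) = 2.51.

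**Where the rules coincide.** Solving bound = 1.984 with t by patients gives about 94 per arm at 25% events, 87 at 35% and 101 at 20%, as well as 90 at 30%.

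**Overall power, 30% events, looks from 50% to 80%.** 80.1% to 80.3% with the fixed threshold; 79.5% to 80.1% with the spending bound.

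**The case against.** The strongest reply is that the section gives one rule and then reports, in the past tense, how its number was obtained. A planned-look value quoted with its generating function is ordinary reporting, and the reproduction at 1.983 supports that reading. Recomputation at the actual look may be laid down in the analysis plan or the monitoring board charter, neither of which is shown. This stands as a reason not to call the two statements an outright contradiction. It does not remove the point, because the article applies the number as a decision threshold at every look it permits, while its derivation supports that number only at the planned one.

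Three stronger readings are tempting, and the documents do not support them.

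- A reader might infer that the rules agree only at exactly 90 per arm with 30% events. They agree along a curve of patient numbers and event rates.
- A reader might infer that any other look makes the trial act against its design. Decisions differ only if the observed odds ratio falls between the two bounds. At 30% events and a look after 50%, the difference can only be that the fixed rule continues where the spending bound stops.
- A reader might infer a loss of error control. The bound that reproduces 1.984 is a futility bound; stopping there cannot raise the one-sided 0.025, and power hardly moves.

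The objection is also right that the low-event bounds depend on an unstated definition of information, and that all the figures presume beta spending and a direction for the odds ratio, neither of which the article gives.

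**Conclusion.** The point holds in a limited form and should be corrected. The threshold of 1.984 is the rho=3.5 futility bound for the planned look with planned events, yet the text applies it unchanged to a look with no upper limit on timing. At 30% events the gap is already 1.984 against 1.84 at a 55% look, and 1.984 against 1.72 at 60%. It matters most when ACH is truly worse: at an odds ratio equal to the margin and a 60% look, the written rule stops about 45% of trials against about 64%. In the other direction, fewer events at 90 per arm raise the chance of stopping equal arms from 1.8% to about 3.3% at an assumed 20% rate.

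The effect is confined to the interim stopping decision. These sizes rest on beta spending, an ACH-over-control odds ratio, the normal approximation, and assumed look times and event rates. If the look falls at 90 per arm with about 30% events, the two rules coincide and nothing changes.

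**What to change.** Either of two changes to the Interim analysis section is enough, with the same wording carried into the analysis plan and the monitoring board charter if they do not already have it.

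- State that the interim decision uses the rho=3.5 boundary on the Z scale, computed at the information fraction actually reached. Name the error being spent and say whether information means patients or statistical information. Give OR 1.984 as the illustrative value for 90 per arm with 30% events.
- Or fix the look at 180 patients with complete follow-up and state the boundary on the Z scale.

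The cost is a sentence or two of text and, under the first option, one recomputation of the boundary at the look. No extra patients or data are needed. The change should be made before the interim data are examined.
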